## Abstract

**Introduction:**

Clinical guidelines recommend extended treatment with dual antiplatelet therapy (DAPT) with ticagrelor 60 mg (twice daily) beyond 12 months in high‐risk patients with a history of myocardial infarction (MI) who have previously tolerated DAPT and are not at heightened bleeding risk. However, evidence on patterns of use and associated clinical outcomes in routine clinical practice is limited.

**Methods:**

ALETHEIA is an observational, multi‐country study, designed to describe characteristics, treatment persistence, and bleeding and cardiovascular (CV) outcomes in post‐MI patients who initiate ticagrelor 60 mg in routine clinical practice (NCT04568083). The study will include electronic health data in the United States (US; Medicare, commercial claims) and Europe (Sweden, Italy, United Kingdom, Germany). Characteristics will be described among patients with and without ticagrelor 60 mg ≥1 year post‐MI. Assuming an a priori threshold of 5000 person‐years on‐treatment is met, to ensure sufficient precision, clinical outcomes (bleeding and CV events) among patients treated with ticagrelor 60 mg will be assessed. Risk factors for clinical outcomes and treatment discontinuation will be assessed in patients with ticagrelor 60 mg and meta‐analysis used to combine estimates across databases. Cohort selection will initiate from the ticagrelor 60 mg US and European approval dates and end February 2020. An estimated total of 7250 patients prescribed ticagrelor 60 mg are expected to be included.

**Discussion:**

An increased understanding of patterns of ticagrelor 60 mg use and associated clinical outcomes among high‐risk patients with a prior MI is needed. The a priori specified stepwise approach adapted in this observational study is expected to generate useful evidence for clinical decision‐making and treatment optimization.

## INTRODUCTION

1

Ischemic heart disease is the leading cause of death worldwide, with myocardial infarction (MI) being the most common form.^1^ Despite optimal secondary prevention therapies, the risk of experiencing another major adverse cardiovascular (CV) event (MACE) in patients who are event‐free 1 year after MI is about 20% in the subsequent 3 years.^2^

Dual antiplatelet therapy (DAPT) with acetylsalicylic acid (ASA) and a P2Y_12_ inhibitor (e.g., ticagrelor, clopidogrel, prasugrel) reduces the risk of CV events.^3^, ^4^, ^5^ Several studies have demonstrated a reduced risk of CV events (e.g., stroke, MI, vascular death, stent thrombosis) in patients treated with DAPT following an acute coronary syndrome (ACS), but with an increased risk of major bleeding when compared to ASA or a P2Y_12_ inhibitor alone.^4^, ^6^ In patients with prior MI or coronary stenting, extended DAPT (i.e., for more than 12 months) is also associated with a significant reduction in the risk of CV events, but a higher risk of major bleeding, compared to ASA alone.^4^, ^5^, ^7^

The P2Y_12_ inhibitor ticagrelor, in combination with low‐dose ASA, is indicated for the prevention of CV events in patients with an ACS or a history of MI. The PEGASUS‐TIMI 54 trial demonstrated a lower risk of MACE with extended DAPT with ticagrelor 60 mg (twice daily) and ASA compared to ASA alone (HR 0.84; 95% CI 0.74, 0.95) in patients with a history of MI.^6^ However, an increased risk of major bleeding versus ASA alone was also observed (HR 2.32; 95% CI 1.68, 3.21). Similarly, the DAPT study demonstrated that extending DAPT with either clopidogrel or prasugrel and ASA for up to 30 months following insertion of a drug‐eluting stent for ACS or stable CAD reduced the risk of MACE (HR 0.71; 95% CI 0.59–0.85) and stent thrombosis (HR 0.29; 95% CI 0.17–0.48), compared to 12 months of DAPT, albeit with an increased risk of moderate or severe bleeding (2.5% vs. 1.6%, *p* = .001).^5^ Clinical guidelines recommend extending DAPT, with ticagrelor 60 mg preferred over clopidogrel or prasugrel, beyond 12 months in high‐risk patients with a history of MI without previous bleeding complications or conditions associated with high‐risk of major bleeding.^8^, ^9^, ^10^

It is well known that patients treated in routine clinical practice may differ from those included in clinical trials, although there are limited observational data on patients initiating ticagrelor 60 mg post‐MI.^11^ Data from routine clinical practice are increasingly recognized as a source of valuable information about patterns of medication use as well as safety and effectiveness profiles of medications used in large, heterogenous patient populations, as a complement to randomized clinical trials.^12^ With growing attention on observational studies, the use of high‐quality electronic health data (EHD) from routine clinical practice and the application of scientifically robust methodology is crucial to ensure that the evidence generated is of sufficient quality to inform decision‐making, as also highlighted by the recent initiatives from regulatory agencies in the United States (US) and Europe.^13^, ^14^

This paper presents the rationale and design of ALETHEIA, an observational study with the primary objective to describe patient characteristics, treatment persistence, and event rates of bleeding requiring hospitalization in a large multi‐country cohort of patients treated with ticagrelor 60 mg after an MI. Additional objectives include to describe event rates for a CV composite outcome (hospitalization for MI or stroke, and all‐cause mortality), and to describe treatment persistence and event rates in patient subgroups. In addition, baseline risk factors associated with bleeding and CV events, as well as with treatment discontinuation, will be explored. To contextualize the characteristics of patients initiating ticagrelor 60 mg, characteristics will also be described for patients treated with a P2Y_12_ inhibitor other than ticagrelor (clopidogrel, prasugrel, or ticlopidine), as well as patients not treated with any P2Y_12_ inhibitor at a similar point in time from their MI as observed among patients initiating ticagrelor 60 mg.

## METHODS

2

### Study design

2.1

ALETHEIA is an observational, multi‐country study using retrospective EHD extracted from multiple sources in the US and in several European countries (Germany, Italy, Sweden, and the United Kingdom [UK]). The full list of objectives is presented in Table 1. The study is registered at www.clinicaltrials.gov (NCT04568083).

**TABLE 1 clc23702-tbl-0001:** Study objectives

Objectives	
Primary	To describe the demographic, clinical, and treatment characteristics of patients initiating ticagrelor 60 mg treatment, at the time of their qualifying MI and at the time of treatment initiation (index date). To describe the persistence and, where feasible, adherence, to treatment with ticagrelor 60 mg, including treatment discontinuation and treatment switch. To describe the cumulative incidence and event rates (incidence rate and all‐event rate) of bleeding requiring hospitalization in patients treated with ticagrelor 60 mg using an on‐treatment approach.^a^
Secondary	To describe the cumulative incidence and event rates (incidence and all‐event rates) of the composite of MI, stroke, and all‐cause mortality in patients treated with ticagrelor 60 mg using an on‐treatment approach.^a^ To describe treatment persistence, event rates of bleeding requiring hospitalization, event rates of the composite of MI, stroke, and all‐cause mortality, and event rates of their respective individual components using an on‐treatment approach, in patient subgroups.^a^ To describe the type and pattern of discontinuation and re‐initiation of antiplatelet drugs used in the subgroup of patients who undergo an elective PCI after the index date.
Exploratory	To analyze the associations between specific patient characteristics assessed at index date and the risk of bleeding requiring hospitalization, and of the composite endpoint of MI, stroke, and all‐cause mortality, and of their respective individual components, for patients treated with ticagrelor 60 mg using an on‐treatment approach.^a^ To describe patient characteristics at the time of MI and at the assigned index date among patients in a non‐ticagrelor cohort who are treated with a P2Y_12_ inhibitor other than ticagrelor (clopidogrel, prasugrel, or ticlopidine). To describe patient characteristics at the time of MI and at the assigned index date among patients in a non‐ticagrelor cohort who are not treated with any P2Y_12_ inhibitor. To describe event rates of bleeding outcomes (intracranial bleeding, gastrointestinal bleeding, and other bleeding requiring hospitalization, fatal bleeding, bleeding not requiring hospitalization), of CV outcomes (recurrent MI, all‐cause stroke, ischemic stroke, CV death, CHD death), all‐cause mortality, and of dyspnea and lower limb amputation in patients treated with ticagrelor 60 mg using an on‐treatment approach.^a^ To conduct sensitivity analyses (for the primary bleeding outcome and the secondary CV composite outcome) for primary objective 3, secondary objectives 1 and 2, and exploratory objective 1 using an intention‐to‐treat approach instead of an on‐treatment approach. ^a^ To investigate the associations between patient characteristics (measured at the index date) and the risk of discontinuing ticagrelor 60 mg.

Abbreviations: CHD, coronary heart disease; CV, cardiovascular; MI, myocardial infarction; PCI, percutaneous coronary intervention.

^a^
The total number of person‐years on treatment in the Primary population will be assessed across all countries. Clinical outcomes in this study will not be analyzed unless the a priori threshold of 5000 person‐years on‐treatment with ticagrelor 60 mg is met in the Primary population, as a total across all data sources.

To maximize patient inclusion and ensure a sufficient look‐back period to appropriately identify eligible patients, the study will span a broad eligibility period from the earliest date of data availability to the most recent data available at data extraction from each database. In general, the eligibility period will begin at least 3 years prior to the ticagrelor 60 mg approval date (European Union [EU]: 19 December 2015; US: 3 September 2015).

### Patient populations

2.2

To account for differences between clinical trial selection criteria and geographic adaptations of labels for ticagrelor 60 mg, the study includes both a Primary and a Secondary population. The Primary population is defined to align as close as possible with the PEGASUS‐TIMI 54 eligible population and the US approved label.^6^ The Secondary population is defined to align as close as possible to the European approved label.^15^, ^16^, ^17^, ^18^ Both study populations will be defined in each data source. For all databases, cohort selection will begin on the US ticagrelor 60 mg approval date for the Primary population and on the EU approval date for the Secondary population. Across databases, the latest date of the cohort selection period will be 29 February, 2020.

The full eligibility criteria are described in Table 2. Briefly, the Primary population will include patients with a first prescription of ticagrelor 60 mg ≥12 months after their most recent hospitalization with a primary diagnosis of MI (i.e., their qualifying MI). The Secondary population will include patients with a first prescription of ticagrelor 60 mg, either (i) 12–24 months following their qualifying MI, or (ii) 12–36 months following their qualifying MI and with P2Y_12_ inhibitor treatment ≤12 months prior to the first ticagrelor 60 mg prescription. The date of the first ticagrelor 60 mg prescription following the qualifying MI will be defined as the index date. The exclusion criteria are based on PEGASUS‐TIMI 54 and include a history of ischemic stroke, intracranial bleeding, hepatic impairment, gastrointestinal bleeding, stage 5 chronic kidney disease (CKD), or renal failure. In recognition that the timing of ticagrelor 60 mg initiation may vary in clinical practice, the study will also include the Anytime cohort, a complementary population comprising patients with a first prescription of ticagrelor 60 mg any time after their qualifying MI.

**TABLE 2 clc23702-tbl-0002:** Study inclusion and exclusion criteria

	Primary population	Secondary population	
Inclusion criteria			
	Hospitalization with a primary diagnosis of MI during the eligibility period	Hospitalization with a primary diagnosis of MI during the eligibility period	
	–	Age ≥ 50 years at the index date	
	–	At least one of the following risk factors assessed at the index date:	
	–	Age ≥ 65 years Diabetes mellitus requiring medication (defined as ≥1 prescription any time prior to the index date) A second prior MI (defined as hospitalization with a primary diagnosis of MI in the baseline period with the date of diagnosis >30 days prior to the date of qualifying MI) Chronic non‐end‐stage renal dysfunction (defined as a diagnosis of CKD stage 1 to 4 in the baseline period)	
	A first prescription of ticagrelor 60 mg ≥12 months following their qualifying MI	A first prescription of ticagrelor 60 mg and one of the following criteria:1) 12–24 months after their qualifying MI, or 2) 24–36 months after their qualifying MI and treatment with an P2Y_12_ inhibitor ≤12 months prior to the first ticagrelor 60 mg prescription	
Exclusion criteria			
	Dies, emigrates, or disenrolls from the database (where applicable) prior to the ticagrelor 60 mg approval date Ineligibility for ticagrelor 60 mg use (restricted to the conditions possible to capture within the data sources)—one or more of the following: Concomitant use of an anticoagulant or a strong CYP3A4 inhibitor or inducer or substrate with a narrow therapeutic index (prescription within 60/90 days prior to the index date) Prior ischemic stroke, history of intracranial bleeding, severe hepatic impairment, CKD stage 5 or renal failure requiring dialysis (any time prior to the index date)		

	Gastrointestinal bleeding (within 6 months prior to the index date) <1 year of data available prior to the qualifying MI (for assessment of patient characteristics at qualifying MI^a^)		

Abbreviations: CKD, chronic kidney disease; CYP3A4, cytochrome P450 3A4; MI, myocardial infarction.

^a^
The qualifying MI is defined as the most recent hospitalization with a primary diagnosis of MI occurring prior to initiation of ticagrelor 60 mg (index date).

To contextualize the characteristics of patients initiating ticagrelor 60 mg, two reference cohorts will be defined, the nonticagrelor P2Y_12_ inhibitor cohort and the non‐P2Y_12_ inhibitor cohort, applying otherwise similar eligibility criteria as for the Primary and Secondary populations. To assign reference patients into these cohorts, the median distribution of time from qualifying MI to index date in the Primary population will first be described. The rationale is to ensure that characteristics of reference patients are described at a similar time from their qualifying MI as for patients initiating ticagrelor 60 mg. Based on this median time, a treatment exposure window will be defined to categorize patients into the respective reference cohorts based on their treatment within this window. The nonticagrelor P2Y_12_ inhibitor cohort will include patients treated with clopidogrel, prasugrel, or ticlopidine at the end of the treatment window. The non‐P2Y_12_ inhibitor cohort will include patients without P2Y_12_ inhibitor treatment at the end of this window. A schematic illustration of all cohorts is presented in Figure 1.

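### The reference cohorts are timed by the Primary population's median alone, so Secondary reference patients may be described at a different time from MI than Secondary initiators

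*Protocol article*

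**What the plan says.** Protocol article, section 2.2, defines two reference cohorts, one on a P2Y12 inhibitor other than ticagrelor and one on none, "applying otherwise similar eligibility criteria as for the Primary and Secondary populations". Their timing is set in sequence. First, "the median distribution of time from qualifying MI to index date in the Primary population will first be described". Then: "Based on this median time, a treatment exposure window will be defined to categorize patients into the respective reference cohorts". Treatment is read when the window closes; the untreated cohort, for example, is "patients without P2Y_12_ inhibitor treatment at the end of this window". The purpose is given as follows: "The rationale is to ensure that characteristics of reference patients are described at a similar time from their qualifying MI" as for the initiators. No Secondary-specific time is mentioned.

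The time criteria in Table 2 differ between the populations:

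- Primary: "A first prescription of ticagrelor 60 mg ≥12 months following their qualifying MI", with no upper limit.
- Secondary, criterion 1: "12–24 months after their qualifying MI".
- Secondary, criterion 2: "24–36 months after their qualifying MI and treatment with an" P2Y12 inhibitor in the 12 months before the first ticagrelor 60 mg prescription.

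The running text of section 2.2 gives criterion 2 as 12–36 months, not 24–36. The Discussion (section 3) adds that reference patients are categorised on treatment at 15 months or later after MI, that this may fall after the index date for some of them, and that the comparable timing is a strength of the study.

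**The concern.** Contextualisation is the only job of the reference cohorts, and it depends on describing them at about the same time from MI as the initiators. For Primary, the anchor comes from the patients being contextualised. For Secondary, it comes from a population that also contains initiators too long after their MI to be in Secondary. Those late initiators can push the anchor later without having any counterpart among Secondary initiators.

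If that happens, differences between Secondary initiators and their reference patients in recent P2Y12 use, age or comorbidity would partly reflect the timing rule and not prescribing choice. The Discussion covers survival bias from the 15-month rule but does not mention this mismatch.

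**Working it through.** The article states no figure on this point (no Primary median, Secondary median or window width), so there is nothing to reproduce. The check is one of logic, followed by a range under stated assumptions.

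**1. Direction.** On timing grounds, the initiators who are in Primary but not in Secondary are those beyond 36 months and, under Table 2, those at 24–36 months without a recent P2Y12 inhibitor. All of them lie beyond 24 months. If recent use is equally common across 24–36 months, removing them can only lower the median or leave it unchanged. The Secondary age and risk-factor criteria could move it either way, and the article gives nothing to judge that by. So the Primary median can be later than the Secondary median, but it need not be.

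**2. Size, under assumptions.** Let m be the Primary median in months. Assume that time from MI to index is 12 months plus an exponential with rate λ = ln 2/(m − 12), so that F(t) = 1 − exp(−λ(t − 12)). Let q be the share of 24–36-month initiators with a P2Y12 inhibitor in the prior 12 months, assumed to be 0.3 or 0.8. Age and risk-factor criteria are ignored.

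- Share of Primary initiators meeting the Secondary time criteria: S = F(24) + q[F(36) − F(24)].
- Secondary median, when it falls in the first band (as it does throughout): 12 − ln(1 − S/2)/λ.

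Example with m = 24: λ = 0.0578, F(24) = 0.50, F(36) = 0.75.

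- q = 0.3: S = 0.50 + 0.3 × 0.25 = 0.575. The median is 12 − ln(0.7125)/0.0578 = 17.9, a gap of 6.1 months.
- q = 0.8: S = 0.70. The median is 12 − ln(0.65)/0.0578 = 19.5, a gap of 4.5 months.

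| Primary median (assumed) | Secondary median | Gap, months | Secondary initiators at 12–24 months |
|---|---|---|---|
| 15 | 14.8–14.9 | 0.1–0.2 | 95–98% |
| 18 | 16.5–17.2 | 0.8–1.5 | 83–93% |
| 21 | 17.3–18.6 | 2.4–3.7 | 76–89% |
| 24 | 17.9–19.5 | 4.5–6.1 | 71–87% |
| 30 | 18.5–20.5 | 9.5–11.5 | 66–84% |
| 36 | 18.8–21.0 | 15.0–17.2 | 64–82% |

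The gap is small at 15–18 months and material from about 24 months.

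**3. Effect of a window.** Suppose reference index dates are spread evenly around the Primary median (assumed widths).

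- Median 21 ± 6 months (15–27): 9/12 = 75% fall in the 12–24 band and 25% in the 24–36 band.
- Median 24 ± 3 months: 50% fall in each band.
- Median 36 ± 3 months: 50% fall in the 24–36 band and 50% beyond 36 months.

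The split between bands therefore depends on the window as well as on the median.

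**4. The branch condition.** If criterion 2 of Table 2 is carried over to reference patients, then a patient in the no-P2Y12 cohort who is indexed at 24–36 months must still have had a P2Y12 inhibitor in the preceding 12 months. In that band the cohort would hold only people who had recently stopped. This follows whether or not index times vary, but only if the condition is carried over, which the article does not say.

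**The case against.** A reader might infer more: that every Secondary reference patient must land in one branch of Table 2, or in none, so that either 0% or 100% fall under criterion 2 and the cohorts cannot match. The article does not support this, for three reasons.

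- It would need one identical index time for all reference patients. The article speaks of a window of unstated width, and the Discussion keeps index date and treatment assessment apart. Step 3 shows that the all-or-nothing result fails once index dates vary across a band limit.
- Both Secondary branches are defined by a first ticagrelor 60 mg prescription, which reference patients do not have. The criteria are said only to be otherwise similar, so literal carry-over is an inference.
- Under the wording in the running text (12–36 months), criterion 2 overlaps criterion 1, so membership of a single branch is not well defined.

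The mismatch may also be small. The Discussion calls the interval between index (12 months or later) and treatment assessment (15 months or later) short. That suggests early timing was expected, but does not establish it. The stated aim is similar timing, not matching. Window width and index assignment may be set out in the full protocol, and their absence from the article is not a fault. The cohorts are exploratory and descriptive (Table 1), and section 2.5 rules out outcome analyses in them.

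All of this limits the size and certainty of the point. It does not remove the point: using the Primary population as the only anchor is a stated rule, and no window width changes where the anchor comes from.

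**Conclusion.** The concern holds in conditional form. The timing rule secures its own rationale for Primary but not for Secondary. Whether this matters depends on a Primary median and a window that the article does not report. The month figures rest on the assumed exponential shape, on q between 0.3 and 0.8, and on leaving out the age and risk-factor criteria; they show a range and are not predictions. Severity is minor: only exploratory tables of characteristics are affected, and no event rate or comparison of outcomes.

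**What to change.** - Derive the exposure window for the Secondary reference cohorts from the Secondary initiators' own time from MI to index, and keep the Primary median for the Primary reference cohorts.
- State how the Secondary time criteria, including the recent-P2Y12 condition, apply at the assigned index date to patients without a ticagrelor 60 mg prescription.
- Report the distribution of time from MI for initiators and reference patients in each population, so that any remaining gap is visible.
- Reconcile the running text of section 2.2 with Table 2 on criterion 2 (12–36 against 24–36 months).

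The cost is a change of wording and one more programmed index assignment on data already extracted. The downside is that some reference patients may have different index dates, or even different treatment classifications, in the Primary and Secondary tables; a table footnote should say so.

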	Medicare health insurance database covers fee‐for‐service claims data of individuals who are aged ≥65 years, select individuals with disabilities aged <65 years, and those with end‐stage renal disease. The data cover beneficiaries' encounters with the healthcare system and receipt of therapeutic interventions, including medications (i.e., date of dispensed prescriptions), procedures, and services. Data on mortality are available.	62 million; 19%	3100
UK	CPRD GOLD contains longitudinal primary care data from over 800 general practices, whereas CRPD Aurum holds anonymized, longitudinal, primary care patient records collected from over 1100 general practices. Data includes information on patient characteristics and issued prescription medicines. HES covers data on diagnoses and procedures for all hospitalization episodes from England, whereas ONS covers information on all‐cause and cause‐specific death. Data from both HES and ONS will be linked to primary care data of the CPRD. After removal of duplicates, GOLD and Aurum primary care databases will be used for the analysis.	13.5 million; 24% (GOLD+Aurum)	250
Sweden	The National Patient Register includes information on hospital discharge diagnoses and procedures. The Swedish Prescribed Drug Register covers data on all prescribed medications purchased at Swedish community pharmacies. The Cause of Death Register includes information on date and cause of death. The registers are linked by the register holder via the unique personal identification number.	10 million; >99%	800
Germany	AOK PLUS covers longitudinal claims data submitted from primary, secondary, and tertiary care, and contains information on patient demographics, inpatient hospitalizations, outpatient visits, procedures, mortality (inpatient and outpatient date of death), and outpatient prescriptions dispensed in pharmacies.	3.5 million; 4%	150
Italy	ReS database includes data on patient demographics, pharmacy‐dispensed prescription drugs, inpatient diagnoses and procedures, and date of in‐hospital mortality. For deaths in the outpatient setting, neither date of death nor cause of death is recorded in ReS.	5.5 million; 10%	1000
**Total estimated number of patients included across databases** ^a^			**7250**

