Fifth, to allow contextualization of patient characteristics, reference cohorts of nonticagrelor patients will be described at a similar time point from their qualifying MI as will be observed among the patients initiating ticagrelor 60 mg. In routine clinical practice, patients treated for ACS may continue being prescribed a P2Y_12_ inhibitor more than 12 months after an MI, despite not being intended for extended antiplatelet treatment. To limit the inclusion of such patients in the nonticagrelor P2Y_12_ inhibitor cohort, categorization of patients into either reference cohort will be based on their treatment at a minimum of 15 months after their qualifying MI. Exposure to nonticagrelor P2Y_12_ inhibitors or lack of exposure to P2Y_12_ inhibitors may therefore be assessed after the index date for some patients, introducing a survival bias to patients in the reference cohort. Although the extent of this bias cannot be quantified a priori, the impact is likely minimal given the short maximum timeframe between the index date (≥12 months post‐MI) and the time of treatment assessment (≥15 months post‐MI). Sixth, while the primary analyses will be conducted using an on‐treatment approach, reflecting events that occur when patients are receiving ticagrelor 60 mg, censoring at treatment discontinuation may introduce bias due to informative censoring. This could occur if the risk of discontinuing treatment is related to the events of interest, thus violating the key assumption in survival analyses that censoring events are random. While difficult to properly account for, the likelihood of such bias being introduced will be assessed by investigating baseline factors associated with discontinuation. To further assess the potential risk of informative bias, event rates will also be calculated using an intention‐to‐treat approach.

In conclusion, despite the increasing recognition of observational studies to inform healthcare decision‐making, knowledge about treatment patterns and associated outcomes in patients treated with ticagrelor 60 mg in routine clinical practice is limited. The multi‐country, observational ALETHEIA study is designed to address this gap. The study objectives and the a priori specified stepwise approach used for outcomes analyses are expected to generate useful insights for clinical decision‐making and treatment optimization.

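### In the Italian database, deaths outside hospital cannot be dated, so the untreated (non-P2Y12) reference cohort can include patients who had already died

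*Protocol article*

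**What the plan says.** Section 2.2 of the Protocol article forms two reference cohorts by treatment status at the end of an exposure window set from the median time between MI and index date. One holds patients on clopidogrel, prasugrel or ticlopidine at that point. The other, the non-P2Y12 inhibitor cohort, "will include patients without P2Y_12_ inhibitor treatment at the end of this window". Both are formed by "applying otherwise similar eligibility criteria as for the Primary and Secondary populations". The Discussion adds that the categorisation "will be based on their treatment at a minimum of 15 months after their qualifying MI".

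Table 3 (section 2.3) says that ReS holds pharmacy dispensings, "inpatient diagnoses and procedures, and date of in‐hospital mortality". It continues: "For deaths in the outpatient setting, neither date of death nor cause of death is recorded in ReS".

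The only exclusion for death is in Table 2, for a patient who "Dies, emigrates, or disenrolls from the database (where applicable) prior to the ticagrelor 60 mg approval date". The Discussion concedes that treatment may be assessed after the index date for some patients, "introducing a survival bias to patients in the reference cohort", and expects the impact to be minimal because the gap is short.

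Table 1 lists the description of both reference cohorts, at the MI and at the assigned index date, among the exploratory objectives.

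**The concern.** A cohort defined by having no treatment record is only sound if a missing record means a living, observable patient who is not treated. In ReS it can also mean that the patient died at home: dispensings stop and no death appears. The stated rule then counts that patient as managed without a P2Y12 inhibitor.

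The Discussion presents the reference cohorts as a strength, because they put the characteristics of ticagrelor 60 mg starters in context and bear on how treatment is selected. Patients who die in the first year or so after an MI can be expected to be older and sicker than those who live. If they are counted as untreated, the Italian contrast could be read as clinicians withholding extended treatment from frail patients when part of it is undetected death.

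**Working it through.** **Do the stated rules remove these patients?**

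- The Table 2 exclusion stops at the ticagrelor 60 mg approval date, not at the end of the window. For undated outpatient deaths in ReS it cannot be applied from death dates at all.
- The restricted meta-analyses in the Discussion deal with missing mortality by leaving out Optum and MarketScan. ReS stays in, and those analyses concern outcomes, which are not analysed in the reference cohorts (section 2.5).
- The survival bias that the Discussion concedes is a different problem. It arises because patients must be alive at assessment, and it is judged small because only about three months separate index date (12 months or later) and assessment (15 months or later). Here patients who are dead are included, and unrecorded deaths accumulate from MI discharge to the window end, which is 15 months or more.

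So no rule in the article removes them.

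**Where do they go?** Someone who died well before the window end has no supply at that point and enters the non-P2Y12 cohort. Someone who died shortly before it, with dispensed supply still running, looks treated and may enter the other-P2Y12 cohort.

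**How large could it be?** The article gives no figure on this point, so there is none to reproduce. Inputs, both assumed:

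- d: among otherwise eligible ReS patients with no recorded death, the share who died outside hospital before the window end; 1% to 8%.
- u: the share of survivors without a P2Y12 inhibitor at the window end; 30% to 70%.

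If all unrecorded deaths fall in the untreated cohort, the share of that cohort who are dead is c = d / (d + (1 − d) × u).

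| d | u = 30% | u = 50% | u = 70% |
|---|---|---|---|
| 1% | 3.3% | 2.0% | 1.4% |
| 3% | 9.3% | 5.8% | 4.2% |
| 5% | 14.9% | 9.5% | 7.0% |
| 8% | 22.5% | 14.8% | 11.0% |

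- Lowest: 0.01 / (0.01 + 0.99 × 0.7) = 0.01 / 0.703 = 1.4%.
- Middle: 0.03 / (0.03 + 0.97 × 0.5) = 0.03 / 0.515 = 5.8%.
- Highest: 0.08 / (0.08 + 0.92 × 0.3) = 0.08 / 0.356 = 22.5%.

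For given d and u these are upper figures, because deaths with supply still running go to the other cohort.

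**Effect on the description, at c = 5.8%:**

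- Age at MI: if those who died were on average 10 years older (assumed), the cohort mean is too high by 0.058 × 10 = 0.6 years. Over the whole table the shift is 0.1 to 2.2 years.
- Comedication at the assigned index date: if the true prevalence is 90% and those who died show no dispensings by then (both assumed), it reads 0.90 × (1 − 0.058) = 85%. Patients who died between index date and window end would still show some medication, so the real drop would be smaller.

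**Weight of Italy.** ReS is projected to supply 1000 of 7250 ticagrelor 60 mg patients, or 13.8%. The article gives no sizes for the reference cohorts.

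**The case against.** The strongest reply is that the article condenses a full protocol. Window length, supply rules and any requirement to be observable at the window end may be set out there, and the cohort schematic is not shown. This has force as to detail, but it does not answer the point. Even a written requirement to be alive at the window end could not be enforced in ReS from death dates; it would need another source or a proxy, and the article names none.

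Second, the article says only that date and cause of outpatient death are missing. It does not say that ReS lacks registration or exit data, and Table 2 uses disenrolment where it applies. If exit dates exist, much of the problem could be solved with them. This stands, and it is why the fix begins there.

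Third, the inputs to the size are all assumed. The upper end needs 8% unrecorded deaths in a population that already excludes several high-risk conditions. This also stands.

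A reader might go further and infer three things that the documents do not support:

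- That the other-P2Y12 cohort is untouched. It is not, because supply can outlast the patient.
- That the bias makes the untreated cohort look uniformly sicker. Age and comorbidity would tend to read high, but comedication at the index date would read low, so the picture is mixed.
- That event rates are distorted by this mechanism. Outcomes are analysed only in the ticagrelor 60 mg cohorts.

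**Conclusion.** The point holds in a limited form. The membership rule and the ReS death data, both as stated, allow patients who died outside hospital to be described as living reference patients. Most would fall in the untreated cohort and some possibly in the other-P2Y12 cohort.

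The expected direction is older and sicker at the MI, and less medicated at the assigned index date. That rests on the assumption that those who die are older and sicker, and that some are dead by the index date. The share of the Italian untreated cohort affected is 1.4% to 22.5% over the assumed inputs, and 5.8% at 3% unrecorded deaths with half of survivors untreated. None of these inputs comes from the documents, so the range shows what is possible and is not an estimate.

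What is at stake is one exploratory description in one of seven databases; no primary or secondary result depends on it. It still deserves correction, because the contrast invites a conclusion about treatment selection that undetected death could partly produce.

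**What to change.** For ReS:

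- State how observability at the window end is established. If registration or exit data exist, require reference patients to be registered at that date.
- If they do not exist, add a sensitivity description of both reference cohorts restricted to patients with any dispensing or hospital record on or after the window end. Show it beside the unrestricted cohorts.
- State the limitation in either case.
- If reference characteristics are combined across databases, repeat the combination without ReS.

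The cost is one selection rule and one extra table, from data already held. The restricted version drops some living patients who have no later contact, including some who stopped all medication and belong in the untreated cohort, so it conditions on later use of health care. It should therefore be shown with the unrestricted description and not replace it.
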